#### Phase III (Intervention Stage)

In the control group, malaria education for the local community was integrated into routine services at the local health center. These educational sessions were provided during the first prenatal visit by pregnant women to the health center, food supplement distribution activities, and immunization programs conducted during integrated service post activities at the village level. These activities were conducted once per month, and malaria-related information was disseminated once per village on average. The primary audience for these sessions included pregnant women, mothers with children younger than 5 years, and young children. Occasionally, malaria education was provided to all individuals attending the health centers. In the intervention group, malaria education followed the same structure as in the control group but was supplemented with a health education campaign targeting the entire village community.

The intervention followed the steps outlined in the following paragraphs.

First, the research team met with the subdistrict head and village leaders in the 2 selected subdistricts designated as the experimental areas. After obtaining their approval, the research team recorded a campaign message delivered by each subdistrict leader. The campaign content, developed by experts in malaria-related behavior, mathematical modeling, and rural development, included the main symptoms of malaria, prevention strategies, and the appropriate treatment-seeking behavior for suspected malaria cases. During the campaign, the subdistrict head occasionally emphasized key points in the local language to improve comprehension. The recorded message was then combined with a locally popular song to enhance engagement. The final recording was 15 minutes long. Second, 6 health promotion staff members from Baing and Mahu Public Health Centers were selected as RAs to play the recording. The recording was broadcast using loudspeakers to ensure wide community outreach. Third, the RAs played the recorded message once per week for 20 weeks in the 13 intervention villages. The intervention started in the fourth week of August 2024 and concluded in the second week of January 2025. In each selected village, the intervention was conducted in 4 different locations per week to ensure that all community members were reached. The principal investigator maintained weekly communication with the RAs to ensure that the intervention was being conducted properly. Over the 20-week intervention period, the research team monitored implementation by visiting the experimental villages once a month for 5 months.

#### Phase IV (Evaluation Stage)

At this stage, the research team conducted a household survey in both the intervention and control groups using the same questionnaire that was administered during the baseline phase of the study. The final data collection was done from the third week of January 2025 to the second week of February 2025. Since the research aims to assess the impact of the intervention on all rural adults, participants surveyed before and after the intervention may differ, depending on respondent availability during the data collection period.

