**Methods:**

This study used a cluster-assigned quasi-experimental design with pretest and posttest assessments in control and intervention groups. The control group, consisting of 12 villages, received malaria education integrated into routine health services provided by local health centers. The intervention group, comprising 13 villages, received the same education as the control group, in addition to a malaria campaign conducted once a week for 20 weeks. Before and after the campaign, a household survey was conducted to assess behavioral aspects of malaria, including general knowledge of malaria, AMTSB, and malaria prevention measures knowledge and practice. Improvement in the malaria awareness index, AMTSB, good level of malaria prevention measure knowledge, and good level of malaria prevention measure practice will be determined based on the difference scores for each index before and after the intervention in both groups. The chi-square test will be used to assess score differences. Binary logistic regression analysis will be conducted to identify key risk factors associated with changes in each index.

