**Results:**

The intervention was conducted from the last week of August 2024 to the second week of January 2025. A total of 894 respondents participated before and after the intervention. The project is currently in progress, with multiple papers being drafted for publication in peer-reviewed journals.

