### Statistical Analysis

All statistical analyses will be conducted using SPSS version 27 (IBM Corp), and *P* values <.05 will be considered statistically significant.

For the first outcome variable, descriptive statistics will be used to summarize participants’ sociodemographic characteristics and environmental variables including gender, age group, SES, education level, family size, distance to the nearest health facilities, village accessibility, and household location. A chi-square test will be applied within each study group (intervention and control) to evaluate the association of basic malaria understanding, basic malaria knowledge, the level of malaria knowledge, and the level of malaria awareness before and after the intervention. Unpaired sample *t* tests will be used to investigate the statistical differences. Comparisons will be performed within groups (pre- and postintervention) and between groups to determine the impact of the intervention [61]. Furthermore, a binary logistic regression model will be used to identify the potential factors associated with malaria awareness in both the intervention and control groups [39].

For the second outcome variables, descriptive statistics will be used to summarize participants’ sociodemographic and environmental characteristics including gender, age group, SES, education level, family size, distance to the nearest health facilities, access to village, and household location for both study groups. A chi-square test will be used to evaluate the association between AMTSB and the sociodemographic and environmental characteristics of participants. Unpaired samples *t* tests will be used to assess the statistical differences. Comparisons will be conducted within and between groups for both pre- and postintervention periods. Moreover, binary logistic regression analysis will be used to identify predictors associated with AMTSB among participants in both study groups [41]. Only predictors that demonstrate statistically significant differences (*P*<.05) will be retained in the final model.

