## Results

The time frame of the project is presented in Table 1.

**Table 1 table1:** Timeline of research phases.

Research phases	January-May 2024	June-July 2024	August 2024-January 2025	February 2025	March 2025-December 2026
Questionnaire and question guide development	✓	—^a^	—	—	—
Ethics approval	—	✓	—	—	—
Training of field workers	—	✓	—	—	—
Household surveys for pretest data	—	—	✓	—	—
Data entry	—	—	✓	—	—
Data analysis	—	—	✓	—	—
Manuscript preparation and submission	—	—	✓	—	—
Intervention in 13 villages	—	—	✓	—	—
Household surveys for posttest data	—	—	—	✓	—
Data entry	—	—	—	—	✓
Data analysis for the final outcome	—	—	—	—	✓
Manuscript preparation and submission	—	—	—	—	✓

^a^Not applicable.

Primary data collection for the baseline survey was conducted between August 2024 and September 2024. A total of 894 rural adults participated in face-to-face interviews in both the intervention and control groups. These participants were drawn from 25 villages across East Sumba District. The intervention commenced in the last week of August 2024 and concluded in the second week of January 2025. The project is currently in the process of drafting multiple research papers, which will be submitted for publication in peer-reviewed journals to disseminate the findings. This study was funded by the Directorate General of Higher Education, Ministry of Education and Culture of the Republic of Indonesia (main contract number: 073/E5/PG.02.00.PL/2024) on June 11, 2024, and an extension contract number from the Research Center of Nusa Cendana University Kupang ENT Province (contract number: 448/UN15.22/SP2H/PL/2024) on June 12, 2024.

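### Before/after change is tested as if the two survey waves were independent, but the design allows the same people or households in both and does not say how the second wave was drawn

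*Protocol article*

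**What the plan says.** **Who is surveyed twice.** Households were randomly sampled within villages (Study Design and Sampling Technique), and the head or any other adult member could answer (Phase II). For the second survey, Phase IV says that "participants surveyed before and after the intervention may differ, depending on respondent availability during the data collection period". It gives as reason that the target is all rural adults. The article does not say whether the second survey went back to the same households or drew new ones.

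**How many.** The abstract's Results state: "A total of 894 respondents participated before and after the intervention". The main Results section first says "Primary data collection for the baseline survey was conducted between August 2024 and September 2024" and then "A total of 894 rural adults participated in face-to-face interviews in both the intervention and control groups". The counts are not split by wave or by arm.

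**How change is tested.** For the awareness outcome, Statistical Analysis plans a before/after chi-square within each group and adds: "Unpaired sample *t* tests will be used to investigate the statistical differences". Then: "Comparisons will be performed within groups (pre- and postintervention) and between groups to determine the impact of the intervention". Nearly the same wording, with unpaired t tests, is used for appropriate treatment-seeking (AMTSB), prevention knowledge (MPMK) and prevention practice (MPMP). The abstract's Methods say that improvement "will be determined based on the difference scores for each index before and after the intervention in both groups". The Outcome Variables section defines improvement for these four outcomes as a higher value after than before.

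**The concern.** An unpaired t test or an ordinary before/after chi-square takes the variance of a change as the sum of the two wave variances. That is right if wave 2 is a fresh sample. If some wave-2 respondents, or their households, were also in wave 1, their answers are likely to be positively correlated. The covariance term is then missing and the standard error of change is not the right one.

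This is a stated choice of test, and it bears on the quantity by which improvement is defined for four primary outcomes. Where the respondent did change, a pre/post difference can also reflect who was available at each visit. The article describes no adjustment of the pre/post contrast for that. A reader cannot tell whether the study is a followed cohort, a repeated cross-section or a mixture, and so cannot judge whether the planned tests suit it.

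**Working it through.** **1. The plan's own figure.** Sample Size Calculation: 1.96² × 0.488 × 0.512 / 0.05² = 383.9, rounded to 384; × 2 = 768; × 1.15 = 883.2, rounded to 884, or 442 per group. The stated figure reproduces. It is a precision calculation for one proportion and contains no pre/post correlation, so it does not settle the question either way.

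**2. Person overlap alone.** Inputs from the article: n = 442 per group per wave, p = 0.488, significance level 0.05 (taken as two-sided). Assumed: f, the share of people in both waves; r, their pre/post correlation; and the same p in both waves.

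- Variance of change = 2 × p(1 - p)(1 - f*r)/n
- Unpaired SE (sets f*r = 0) = sqrt(2 × 0.488 × 0.512 / 442) = 0.0336
- Ratio of unpaired to true SE = 1/sqrt(1 - f*r)
- Actual test size = 2 × [1 - Phi(1.96/sqrt(1 - f*r))]

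| f | r | f*r | true SE | unpaired SE too large by | actual size |
|---|---|---|---|---|---|
| 0 | any | 0 | 0.0336 | 0% | 0.050 |
| 0.5 | 0.3 | 0.15 | 0.0310 | 8.5% | 0.034 |
| 0.5 | 0.5 | 0.25 | 0.0291 | 15% | 0.024 |
| 1 | 0.3 | 0.30 | 0.0281 | 20% | 0.019 |
| 1 | 0.5 | 0.50 | 0.0238 | 41% | 0.006 |

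In power terms, take an assumed rise from 48.8% to 58.8% with f = r = 0.5. The unpaired SE is 0.0334 and the true SE 0.0289. Power is Phi[(0.1 - 1.96 × 0.0334)/0.0289] = 88% with the unpaired test, and Phi[0.1/0.0289 - 1.96] = 93% with the overlap modelled.

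A revisited household with a different respondent acts in the same way, with its own value of r.

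**3. Village clustering alone.** Respondents per village per wave: m = 884/25 = 35.4. Assume an intracluster correlation ICC, a between-wave correlation c of village effects, and no repeat respondents. The true variance of a within-arm change, relative to the one the unpaired test uses, is 1 + (m - 1) × ICC - m × ICC × c.

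- ICC 0.05, c = 1: 0.95; SE ratio (true/unpaired) 0.97, actual size 0.044
- ICC 0.05, c = 0.8: 1.30; SE ratio 1.14, actual size 0.086
- ICC 0.05, c = 0: 2.72; SE ratio 1.65, actual size 0.234
- ICC 0.01, c = 0: 1.34; SE ratio 1.16, actual size 0.091

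Step 2 makes the unpaired SE too large and step 3 can make it too small. The article gives none of f, r, ICC or c, so the net error cannot be signed.

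**The case against.** The strongest reply is that this is a repeated cross-section, for which tests unpaired at person level are the consistent choice. Phase IV justifies different respondents by the target population. Data Collection Methods has the same enumerators recruiting at both phases, and the sample size is offered as a guide to recruitment for a survey done twice. This reading is reasonable, and with f = 0 there is no person-overlap error. But other features fit a followed sample: difference scores in the abstract, and the eligibility rule against planned relocation within 6 months (which could equally serve to secure exposure to the campaign). Saying that participants may differ does not rule out that many are the same. Independence is possible but not secured.

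A reader might infer that the article contradicts itself about the 894. It does not clearly do so. The abstract's sentence can mean 894 at each wave rather than the same people twice, and in the main Results the word both refers to the two groups. The count is ambiguous, no more.

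A reader might also infer that nothing adjusts for a changed respondent mix. That goes too far: logistic models with sociodemographic predictors are planned. They are described as identifying associated factors, however, and no wave or arm-by-wave term is mentioned.

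It also stands that positive overlap costs power rather than creating false positives, and that a between-arm comparison at a single time point is not affected by person overlap.

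**Conclusion.** The point holds conditionally. The stated tests for within-group change assume independent waves, and the described design does not guarantee them. On person overlap alone the unpaired standard error is too large by 0% (f*r = 0) to 41% (f*r = 0.5), with 20% at f*r = 0.3. The upper figure needs, for example, full overlap with r = 0.5, which fits poorly with the Phase IV wording.

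Two stronger conclusions are not supported. The standard errors cannot be called wrong outright, because with a fresh second sample the overlap error vanishes. Nor can the tests be called conservative: the test sizes below 5% in the first table hold only if village clustering is ignored, and clustering alone could raise the size to 0.234 under an assumed ICC of 0.05. The net direction is unknown. All values of f, r, ICC and c are assumptions. The point deserves correction because one analysis is suitable whatever the overlap turns out to be.

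**What to change.** For each pre/post outcome (awareness, AMTSB, MPMK, MPMP), replace the separate unpaired tests with one model containing arm, wave and arm-by-wave, adjusted for respondent age, sex and education. The arm-by-wave term estimates the campaign effect directly. Use random effects or cluster-robust standard errors that cover repeat persons or households within villages and the higher clusters. Link persons or households across waves where identifiers exist. Where they do not, cluster at village level or above, which also covers repeat respondents because they sit in the same cluster. With 25 villages in 4 subdistricts, use a small-sample correction and acknowledge that the subdistrict level can be estimated only poorly.

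In the text, state whether wave-2 households were redrawn or revisited, report how many respondents or households were repeated where this is known, give n per wave and arm, and reword the two sentences that carry the 894.

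Cost: some extra analysis work and no new data. Table 1 places the final analysis in March 2025 to December 2026. The precision gain from pairing is available only where identifiers can be linked, and the article does not say that they can.

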### Data Collection Methods

Data were collected in face-to-face interviews, guided by a questionnaire adapted from a previously published study [67]. The questionnaire consists of 5 sections covering demographic characteristics, general knowledge of malaria, treatment-seeking behavior, practice of malaria prevention measures, and practice of malaria treatment-seeking behaviors. Each section contained questions to capture key behavioral aspects of malaria. A detailed list of the questions for each section is provided in Multimedia Appendix 1. Furthermore, this data collection was conducted by local nurses and health promotion workers from the selected health centers. These enumerators participated in a 1-day intensive training to improve their understanding of the study background and objectives. Moreover, enumerators were trained how to approach the potential participants in this study and how to conduct the interview following the guidance of this study and local culture. The same enumerators were responsible for recruiting participants during both baseline data collection and the postintervention phase. For secondary data collection, malaria register books from each public health center were reviewed to obtain data on the number of malaria cases and malaria-related deaths over a 10- year period from 2013 to 2023. Data on the number of malaria cases in each public health center throughout the district were collected from the Health Department of East Sumba District for the same period.

### Independent Variables of the Study

This study considers demographic and environmental factors as independent variables. Demographic variables include gender, age, education level, occupation, and socioeconomic status (SES). Respondents’ SES will be measured based on ownership of durable assets such as a television, refrigerator, car, electricity, telephone, and radio; the number of bedrooms; and home infrastructure conditions such as access to drinking water sources and the presence of water channels around the house [68]. Using principal component analysis, respondents’ SES will be categorized into 5 quantiles ranging from the lowest (quantile 1) to the highest (quantile 5) [69]. Environmental variables in the study include the location of the residence, categorized as rice fields, coastal areas, or hilly areas, and accessibility to villages, classified as easy, moderate, or difficult to access. Additionally, the study considered proximity to health facilities, including the type and distance of the nearest health facilities. For secondary data from the health center, patient records from 2013 to 2023 were reviewed for all patients with suspected malaria, and positive or negative cases were confirmed based on laboratory examination results. The number of malaria cases based on gender, age group, type of *Plasmodium*, time (year and month), location of residence, and type of treatment and the number of deaths since the period under review were collected from the 4 selected health centers.

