The seventh outcome variable in this study is variation in access to basic drinking water and its associated factors among rural communities in ENT Province, Indonesia. Household access to basic drinking water is defined based on the WHO Joint Monitoring Program guidelines, which classify water sources into 4 categories: no service, unimproved, limited, and basic [75]. To analyze this variable, a dichotomous classification will be used, where households will be categorized as either having access to an improved drinking water source (Yes=1) or lacking access to an improved drinking water source (No=0). This classification will help determine disparities in access to safe drinking water and identify key factors influencing these differences.

The secondary outcomes of this study are derived from the analysis of patient medical records from 4 selected health centers, along with additional data from the Department of Health, East Sumba District. The eighth outcome variable focuses on the monthly number of malaria cases recorded over the past 10 years, from 2013 to 2023. By integrating data from both health centers and the Meteorological Agency of East Sumba, this study aims to explore the impact of climatic variables on malaria case fluctuations in this region, following the methodology of a previous study [76]. This analysis will provide valuable insights into seasonal and long-term trends in malaria transmission, which could help inform future malaria prevention and control strategies.

The ninth outcome variable in this study examines the demographic variations in malaria prevalence among communities residing in hilly and coastal areas over the past 10 years (2013-2023). Among the 4 selected health centers, Baing and Nggongi Public Health centers are located in coastal areas, whereas Mahu and Kananggar Public Health Centers are situated in hilly regions. Given that vector distribution and species composition may vary between different geographic settings [77], previous studies in Indonesia have reported significant differences in malaria prevalence between coastal and hilly areas [78]. By analyzing malaria case records from these health centers, this study aims to assess regional disparities in malaria burden and determine how demographic and environmental factors contribute to these differences. This information may help tailor malaria prevention and control efforts to the specific needs of different geographic regions.

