For the sixth outcome variable, participants’ sociodemographic characteristics, environmental variables, and behavioral aspects of malaria in each group will be reported using descriptive statistics. The association between a good level of MPMP and its predictors will be investigated using chi-square tests. Unpaired samples *t* tests will be used to investigate the statistical differences. Comparations will be performed within and between groups for both pre- and postintervention periods. Moreover, binary logistic regression analysis will be performed to identify the primary risk factors influencing MPMP [73,74] among rural communities in both study groups.

For the seventh outcome variables, descriptive statistics will be used to summarize participants’ sociodemographic characteristics, environmental variables, and malaria-related behaviors based on their source of drinking water. The associations between access to improved drinking water and its predictors will be assessed using chi-square tests. Furthermore, a binary logistic regression model will be used to determine predictors influencing access to improved drinking water [75].

For the eighth outcome variable, descriptive analyses of climatic factors across different subdistricts will be performed. Data will be aggregated at the subdistrict level, and statistical estimates will be generated for each variable. Specifically, the total number of malaria cases and the average malaria incidence will be computed. Climatic variables, including maximum, minimum, and mean temperature values, will be calculated. Moreover, data from all 22 subdistricts will be analyzed, focusing on malaria cases and climatic parameters, including maximum, minimum, and average temperature values. To depict the seasonal dynamics, seasonal variations in climatic parameters and malaria cases will be plotted, covering the 2 main seasons. A time series for both predictor and outcome variables will be plotted to deliver an overall perspective. A map of malaria cases will be generated. Scatterplots will be developed to illustrate relationships between malaria cases and predictor variables, following the methods of a previous study [76].

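### The SES index includes drinking-water access and is then a predictor of drinking-water access (outcome 7), so part of that association is built in

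*Protocol article*

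**What the plan says.** Three sections of the protocol article have to be read together.

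- **Independent Variables of the Study.** SES is measured from durable assets, number of bedrooms and "home infrastructure conditions such as access to drinking water sources and the presence of water channels around the house". The scoring rule is: "Using principal component analysis, respondents’ SES will be categorized into 5 quantiles ranging from the lowest (quantile 1) to the highest (quantile 5"). SES belongs to the study-wide list: "Demographic variables include gender, age, education level, occupation, and socioeconomic status (SES"). No outcome is exempted.
- **Outcome Variables.** The seventh outcome is "variation in access to basic drinking water and its associated factors among rural communities in ENT Province, Indonesia". For analysis it is made binary: "households will be categorized as either having access to an improved drinking water source (Yes=1) or lacking access to an improved drinking water source (No=0"). The same section counts it among the seven primary outcomes.
- **Statistical Analysis.** For outcome 7, participants' sociodemographic characteristics, environmental variables and "malaria-related behaviors based on their source of drinking water" are described. Predictors are tested by chi-square, and then "a binary logistic regression model will be used to determine predictors influencing access to improved drinking water". In the same section, the paragraphs on the first two outcomes name SES among the sociodemographic and environmental characteristics.

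**The concern.** One ingredient of the SES predictor measures the same thing as the outcome. A household with a good water source scores higher on SES because of that source, and the model then asks whether higher SES goes with a good water source. Some of the answer is fixed before any data are seen.

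Two things are at stake. The SES odds ratio for outcome 7 would be too large, and a reader would take it as a socioeconomic gradient in water access. The adjusted odds ratios of predictors correlated with SES, such as education, can also shift, because the contaminated index absorbs part of the variation in the outcome.

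**Working it through.** **The plan's own figure.** The article states no number on this point, so there is none to reproduce. The check is a reading of the definitions followed by an illustration of size.

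**Step 1: does the overlap follow from the text?** Water access is a named SES item. SES is an independent variable for the whole study. Outcome 7 is water access, modelled on its predictors. No section states an exclusion. The overlap follows.

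**Step 2: why it biases the association.** Let the items be standardised, z_j, with first-component weights v_j and eigenvalue λ. The SES score is S = Σ v_j z_j. For the water item w,

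Cov(S, z_w) = Σ_{j≠w} v_j r_jw + v_w = λ v_w.

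The lone term v_w is the water item's correlation with itself. Its share of the total is v_w / (λ v_w) = 1/λ. The weaker the common factor among the assets, the larger this built-in share.

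**Step 3: illustration.** Assumptions (none is in the documents): 8 other binary items plus water, all at 50% prevalence, and a latent correlation between the other items of 0.2 or 0.4. From the article: n = 894 and a two-sided 0.05 level. Each setting had 400 runs, with quintiles cut on the first component. Odds ratios (ORs) are medians for water access, top versus bottom quintile.

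| Item correlation | Water–wealth correlation | OR, water left out | OR, water in | Chi-square P<.05, left out | Chi-square P<.05, in |
|---|---|---|---|---|---|
| 0.2 | 0 | 1.01 | 1.11 | 4% | 50% |
| 0.2 | 0.1 | 1.41 | 3.15 | 24% | 89% |
| 0.2 | 0.2 | 1.99 | 5.27 | 81% | >99% |
| 0.2 | 0.3 | 2.75 | 8.75 | >99% | 100% |
| 0.4 | 0 | 1.02 | 1.08 | 3% | 43% |
| 0.4 | 0.1 | 1.51 | 2.03 | 31% | 90% |
| 0.4 | 0.2 | 2.19 | 2.98 | 93% | 100% |
| 0.4 | 0.3 | 3.26 | 4.50 | 100% | 100% |

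Over correlations 0.1 to 0.3 the inflation factor is 3.15/1.41 = 2.2 up to 8.75/2.75 = 3.2 with weakly related assets. It is 2.03/1.51 = 1.3 up to 4.50/3.26 = 1.4 with more strongly related assets.

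This agrees with Step 2. For binary items at 50% prevalence, the observed correlation is (2/π)·arcsin(latent correlation), which gives 0.128 and 0.262. The eigenvalue of the eight assets is then about 1 + 7 × 0.128 = 1.90 or 1 + 7 × 0.262 = 2.83. The built-in share is about 1/1.90 = 53% or 1/2.83 = 35%.

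With no true link, the median odds ratio stays near 1 because the sign of the water item's weight varies from run to run. In any single data set, however, a spurious gradient in one direction or the other is common, as the 43% to 50% rejection rates show.

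**Step 4: other assumed set-ups.** With seven assets of prevalence 0.06 to 0.75, a four-level bedroom count, asset loadings of 0.5 to 0.7 and 300,000 households, odds ratios of 2.0 to 2.2 became 2.6 to 4.3 (water loading 0.2), and 2.8 to 3.3 became 4.8 to 9.7 (water loading 0.3). Two further set-ups at n = 894 gave null rejection rates of 38% to 46% against 5% to 7%, and of about 58% to 60% against about 5%. In a multivariable version with an education variable correlated with wealth, the adjusted odds ratio for education moved from 1.04 to 1.21 without the water item to 0.93 to 1.04 with it.

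**The case against.** The strongest counter-case has five parts.

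- **SES is not named in the outcome 7 paragraph.** That paragraph speaks only of predictors, so SES as a predictor is an inference. This is true, but SES sits in the study-wide list of independent variables and is counted among participant characteristics elsewhere in the same section. Leaving it out would need an exclusion that the article does not state.
- **The two water variables may not be coded alike.** The outcome rests on an international classification of water sources. The coding of the SES item and the questionnaire are not shown. This stands: the overlap may be full or partial, so the association is partly, not wholly, built in.
- **A full analysis plan might drop the item for this outcome.** That is possible. But the article itself fixes the SES components, the scoring method, the outcome and the model, and those stated choices conflict as they stand.
- **The size rests on assumptions.** This stands. Only the direction is firm, and only if water access is positively related to wealth.
- **The consequence is narrow.** None of the four study objectives concerns drinking water, and the outcome 7 analysis contains no intervention comparison. This also stands and limits the weight of the point. Even so, the article lists outcome 7 as primary and intends to report factors behind differences in water access.

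**Conclusion.** The concern holds. Followed as written, the outcome 7 analysis gives a biased SES association, because water access sits on both sides of the model. Under the assumed item structures, and with a water–wealth correlation of 0.1 to 0.3, the top-versus-bottom quintile odds ratio is inflated by a factor of about 1.3 to 3.2. With no true link, the chi-square test for SES is significant in roughly 40% to 60% of data sets instead of about 5%. Shifts in correlated predictors such as education are smaller but can move an adjusted odds ratio across 1.

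The conclusion assumes that SES enters the outcome 7 analysis as the study-wide list implies, and that the SES water item overlaps at least partly with the outcome. The true size depends on the loadings in the collected data. Outcomes 1 to 6 and the register-based outcomes are not touched.

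**What to change.** For outcome 7 only, rerun the principal component analysis without the drinking-water item. Also leave out the water-channel item: it is not part of the outcome definition, but it is close enough to household water infrastructure that dropping it is the cautious choice. Recut the quintiles and use them in the descriptive table, the chi-square tests and the logistic model. State in the methods that this index differs from the one used for the malaria outcomes, where the full index can stay. A version that keeps the water-channel item can be shown as a sensitivity analysis. If a reduced index is not wanted, dropping SES as a predictor of outcome 7 also removes the circularity, but loses a predictor of interest.

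The cost is one extra principal component run on data already collected, with no change to design or fieldwork. The timeline table shows some analysis and manuscript work during August 2024 to January 2025. If outcome 7 has already been analysed with the full index, it should be rerun before it is reported.
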